#### Phase 2: Implementation, Economic, and Developmental Evaluation

The evaluation is a pragmatic, real-world implementation and developmental evaluation design to support feasibility. A developmental evaluation approach, in which evaluation questions are used to support decision making and modifications to improve interventions and programs [59], allows for iterative modification of the intervention based on collected data. This method has been successfully adopted to evaluate the ePRO tool [46].

### Study Design

We will conduct a nonrandomized controlled trial to understand the impact of the intervention. For each site (SHS and THP) and each service (acute medicine and rehab), half of the participating wards will be designated as control while the other half will be designated as intervention (4 wards per hospital for a total of 8 wards). Quasi-experimental (or nonrandomized) design is often used in medical informatics evaluation due to insufficient sample size for cluster-randomized design [60] and complexity of intervention [61]. We have chosen to designate intervention wards together with operational leaders at each organization rather than randomize wards to increase the chance of successful implementation. While this could introduce selection bias into the study, it is felt this risk is worthwhile given that one important barrier to adoption of information communication technologies in hospitals is lack of readiness for implementation [62-64]. If clinical units that are not ready to take on a new technology implementation are randomized into the intervention group, we may experience a feasibility barrier that could derail the study before it begins. Our mixed-methods approach has been designed to capture important characteristics of the included clinical wards so that any potential selection bias can be understood.

General medicine units at both organizations serve a complex and clinically diverse population, with a median age of 73 (IQR 57-84) years and a median of 6 (IQR 3-9) coexisting medical conditions [65]. They care for patients with a wide variety of diagnoses (more than 200 distinct diagnoses) with the top 10 diagnoses comprising 36.2% of hospitalizations [66]. Rehabilitation services across the two organizations admit patients due to stroke, musculoskeletal concerns, and complex medical needs. At THP, services are not diagnosis-based; at SHS, however, patients are clustered on wards with specialized services.

We will collect baseline data from all wards (control and intervention) during phase 1 while co-design is ongoing and the intervention has not been deployed. During phase 2, after co-design is complete, the co-designed technology intervention and workflow will be rolled out to only the intervention wards. We will then collect data (identical to what was collected at baseline) from all wards (control and intervention) to understand the impact of technology by examining the differential change in control and intervention wards between baseline and intervention periods (difference in differences approach).

### Population and Recruitment

Patients will be recruited at the time of admission to one of the services (acute medicine or rehab) in the study. Patients aged 60 years and over, with CCN defined as presenting with 3 or more chronic conditions from the 16 most prominent in the population: arthritis (except rheumatoid arthritis), chronic coronary syndrome, dementia, hypertension, cardiac arrhythmia, rheumatoid arthritis, asthma, osteoporosis, stroke, depression, chronic obstructive pulmonary disease, acute myocardial infarction, diabetes, congestive heart failure, cancer, and renal failure.

This method is aligned with current and established methods to identify patients with CCN [67-69]. Patients must be slated to be discharged home. As the technology is only currently available in English, patients (or a caregiver) must be able to speak and read English. Patients with mild cognitive impairment will not be excluded if able to provide informed consent and engage with the intervention (independently or with caregiver aid). During phase 1, all recruited patients will receive usual care. During phase 2, recruited patients from the intervention wards will receive the Digital Bridge intervention while those from control wards will receive usual care. Family/caregivers of recruited patients may be invited to participate in qualitative interviews.

As workflow integration is a foundation for implementing technology, all hospital providers on the general medicine and rehabilitation services will be invited to participate. PCPs of recruited patients will be contacted and invited to participate while the patient is still in hospital. Recruited patients may still participate in the study if their PCP does not wish to participate or if they do not have a PCP at the time of study enrollment. Should the PCP choose to join, they will be consented and trained to adopt the technology to support their patients post-discharge if their patients were recruited from the intervention wards during phase 2.

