		**Patients and caregivers**					
			CFIR^j^ characteristics of individuals: demographics, level of complexity, social supports, comfort with technology	Patient information sheet		At recruitment	
			Self-efficacy, other relevant characteristics (eg, health literacy)	Focus groups (patients)		1 and 6 months post-discharge	
			CFIR process: patient-provider relationship, service frequency (what services from whom at what time points?)				
				Observation (discourse analysis)		Interactions in hospital and in community	
				Focus groups (patients)		1 and 6 months post-discharge	

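### For patients with mild cognitive impairment, eligibility is tied to an intervention present in only one of the four ward-by-period cells, so the primary difference in differences is open to a small selection shift

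*Protocol article*

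**What the plan says.** All references are to the protocol article.

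- **General criteria** (Population and Recruitment): "Patients aged 60 years and over, with CCN defined as presenting with 3 or more chronic conditions from the 16 most prominent in the population". Patients must also be expected to go home, and there is a language condition: "As the technology is only currently available in English, patients (or a caregiver) must be able to speak and read English". One set of criteria is given for all wards and both phases.
- **Subgroup condition** (same section): mild cognitive impairment is not a ground for exclusion "if able to provide informed consent and engage with the intervention (independently or with caregiver aid").
- **Timing** (same section): "Patients will be recruited at the time of admission to one of the services (acute medicine or rehab) in the study".
- **Exposure** (same section): "During phase 1, all recruited patients will receive usual care". In phase 2 only intervention-ward patients receive the Digital Bridge.
- **Design** (Study Design): wards are designated with operational leaders, not randomised. Baseline data are collected during co-design, before anything is deployed. The effect is estimated by "examining the differential change in control and intervention wards between baseline and intervention periods".
- **Outcome** (Table 1; Sample Size Calculation): CTM-3 is taken once, 1 to 2 weeks after discharge, from separate groups of baseline and intervention-period patients.
- **Recruitment data** (Table 1, Patients and caregivers): the patient information sheet records "demographics, level of complexity, social supports, comfort with technology".

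**The concern.** Ability to engage is defined by reference to the intervention, but only one of the four cells contains it. On a phase 2 intervention ward the judgement has consequences, because an enrolled patient must be brought onto the tools and supported with ePRO for 6 months after discharge. On a control ward, or on any ward at baseline, a generous judgement costs nothing, and at baseline the workflow to be judged against is unfinished. The article does not say how the condition is to be applied where no intervention is delivered.

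Recruiters know the ward and the period, so they could be stricter in the one cell where the answer matters. Difference in differences removes stable differences between wards and time trends common to both ward types. It does not remove a change in case mix confined to intervention wards in period 2. CTM-3 is measured once in different patients, so there is no within-patient change to absorb such a shift. If the patients not enrolled would have rated their transition lower, part of any apparent CTM-3 gain would come from who was recruited. Study Design acknowledges selection bias from designating wards, but not from this condition.

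**Working it through.** The article gives no figure for this bias, so there is none to reproduce. The planned effect and SD serve only as yardsticks.

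**Inputs from the article**
- Planned CTM-3 increase 13 to 14 points, SD 21.4 (Sample Size Calculation).
- 300 baseline and 300 implementation patients (Abstract), with half the wards in each group (Study Design). If recruitment is even, that is 600 / 4 = 150 per cell.

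**Inputs assumed, because the article gives none**
- m, share of otherwise eligible patients with mild cognitive impairment: 5% to 30%.
- e, extra share of those patients not enrolled in the phase 2 intervention cell: 25% to 100%.
- g, CTM-3 points by which impaired patients score below the others: 5 to 20.

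**Formula**
1. If unimpaired patients average A, a cell with impaired share m averages A − m × g.
2. Losing an extra share e of impaired patients changes that share to m′ = m(1 − e) / (1 − m × e).
3. The cell mean rises by g × (m − m′).
4. The estimate is (I2 − I1) − (C2 − C1), where I and C are intervention and control wards and 1 and 2 the periods. Only I2 moves, so the whole rise passes into the estimate.

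**Results**

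| m | e | g | m′ | Shift (points) |
|---|---|---|---|---|
| 10% | 50% | 10 | 0.05 / 0.95 = 5.26% | 10 × 0.0474 = 0.47 |
| 20% | 50% | 10 | 0.10 / 0.90 = 11.11% | 10 × 0.0889 = 0.89 |
| 5% | 25% | 5 | 0.0375 / 0.9875 = 3.80% | 5 × 0.0120 = 0.06 |
| 30% | 100% | 20 | 0% | 20 × 0.30 = 6.0 |

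The first two rows are mid-range and the last two are the extremes. The shift is exactly zero if e = 0 or g = 0, and its sign reverses if impaired patients score higher than the others.

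**Against the yardsticks**
- Mid-range: 0.47 / 14 = 3.4% to 0.89 / 13 = 6.8% of the planned effect.
- Upper extreme: 6.0 / 13 = 46%, which requires every impaired patient to be lost in that cell and a 20-point gap.
- Standard error of the difference in differences, ignoring clustering: 21.4 × √(4 / 150) = 3.49 points. The mid-range shift is well inside this, but unlike the standard error it does not shrink as more patients are recruited.

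**The case against.** The strongest reply is that the clause is permissive and narrow. It concerns one subgroup, and help from a caregiver satisfies it. A reader might infer that eligibility in general turns on engaging with the intervention; the full sentence does not support that. Nor do the documents say that the condition is met by default on control wards or at baseline. As written it applies everywhere. The language requirement beside it also stems from the technology and is imposed on patients who will receive usual care. Ability to engage can be judged prospectively at admission. Both component technologies are already in use, and the article sets out six functionalities and an anticipated workflow, so staff have some basis for judging. All of this stands, and it limits the point to a risk.

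A reader might also add general refusal of a more demanding study on intervention wards and so reach a larger bias. The documents do not support that here. What control and baseline patients are asked to consent to is not shown, and refusal is a separate mechanism that this clause does not cause.

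Finally, checklists, screening logs and covariates are commonly left to the full protocol or analysis plan, so their absence from an article is no finding. That is right. What remains is the wording of a criterion the article does state: it names something absent from three cells and sets no common way to judge it.

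**Conclusion.** The point holds as a weakness in a stated criterion. It does not show that the primary effect is biased. The subgroup condition can be applied unevenly, recruitment is open to that, and the planned contrast would not correct it.

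The likely size is modest: about 0.5 to 0.9 points mid-range and about 0.06 to 6 points over the wider range, against a planned 13 to 14. These figures rest on three assumed inputs, none of them in the article, and on patients not enrolled scoring lower on CTM-3, which is plausible but unproven. If the condition is applied equally in all cells, there is no shift.

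**What to change.** 1. For patients with mild cognitive impairment only, replace the reference to engaging with the intervention by one check that does not depend on it. An example is being able to complete the study questionnaires and use a web or tablet tool, alone or with a caregiver. Make the check before consent, in the same way on every ward in both periods. Do not extend it to all patients, because that would narrow the broad eligibility that Strengths and Limitations counts in the study's favour.
2. Log eligible, excluded and declined patients by ward and period. The log must run during screening, because exclusions not recorded then are hard to reconstruct.
3. Adjust the CTM-3 difference-in-differences model for the recruitment-sheet items already collected: demographics, level of complexity, social supports and comfort with technology. This reduces imbalance on what is measured, not on what is not.

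The cost is a short checklist and a log on all wards, and possibly a few more exclusions within this subgroup in the control and baseline cells. The covariates need no new data collection.

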### Study Measures

#### Developmental and Economic Evaluation Measures

Our primary outcome is the Care Transitions Measure–3 (CTM-3), a patient-reported measure of transition quality focusing on person-centeredness and communication. The CTM-3 has been validated in similar patient populations transitioning from hospital to home and primary care and in a systematic review of transitions measures was deemed to be the most acceptable measure of quality transitions [70]. To capture likely downstream impact, we will collect secondary outcomes including number of days at home (as a measure of readmissions), goals achieved (captured through the ePRO Goal Attainment Scale), and health-related quality of life (Assessment of Quality of Life–4 Dimensions [AQoL-4D], a brief survey validated in similar populations with demonstrated responsiveness and predictive validity with regard to entrance to long-term care [71,72]).

Team and provider level processes most relevant to this study are measures of communication and relational aspects of teamwork. Relational coordination is “a mutually reinforcing process of communicating and relating for the purpose of task integration” and is measured with a validated instrument consisting of 4 communication domains (frequency, timeliness, accuracy, problem solving) and 3 relational domains (shared goals, shared knowledge, respect) [73]. High relational coordination has been associated with improved patient functioning and quality of care and reduced pain and length of stay [74,75]. Relational coordination will be measured across 4 groups (hospital physicians, nursing, all allied health involved, and PCP) with care transition as the work process. We will administer the relational coordination survey to hospital clinicians at baseline and 1 and 6 months postdeployment. PCPs will be surveyed at enrollment and 1 and 6 months. We recognize using the Digital Bridge for care transitions may be rare events for individual PCPs; their views on communication and relationship with inpatient clinicians will be explicitly captured during interviews in addition to relational coordination surveys.

To determine cost-effectiveness in relation to outcome and process measures, an economic evaluation will be conducted to compare costs and outcomes among patients who transitioned out of hospital using Digital Bridge with the control patient group. Control and intervention patients will be followed for 1 year. Costs will be estimated from a societal perspective. Health services utilization and health system costs will be measured for 1 year using province-wide health system administrative data. Over 85% of total direct costs can be measured using a cost methodology for health administrative data implemented at ICES [76]. System utilization measures will include hospital admission, emergency department visits, days in acute care, 30-day readmissions, primary and specialty care visits, labs, diagnostic imaging, and 7-day post-discharge primary care follow-up. Out-of-pocket costs will be estimated using a patient survey. Caregiver time costs will be estimated using the average industrial wage. Total costs will include the sum of health system costs and out-of-pocket costs. Resources and costs required to design and implement Digital Bridge will be estimated through a project budget review.

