		**Patient (outcomes)**					
			Transition quality	CTM3^d^		1 to 2 weeks post-discharge	
			Health-related quality of life	AQoL-4D^e^		At 1 and 6 months post-discharge	
			Goal attainment	GAS^f^		As captured by ePRO^g^ (intervention only)	

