		**Value for money**					
			Health system utilization and costs	ICES^i^		Utilization 1 year after discharge	
			Patient-reported costs	Patient cost survey		At 1 and 6 months post-discharge	
	**What are the implementation enablers and barriers to adopting technology in this process from patient, caregiver, provider, organizational, and system perspectives?**						

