**Figure 4 figure4:**
[figure not shown]
Within and between group pre-post analysis.

For quantitative outcome measures (eg, CTM-3, relational coordination, AQoL-4D), statistical comparisons between the pre- (baseline) and post- (intervention) data will be made using mixed-effects regression models to account for potential clustering effect of patients from the same service. As this is a complex intervention and local context/implementation factors may affect outcomes, we will perform sensitivity analysis and examine each of the participating services separately. For repeated measures within the same individual, we will use a difference in differences approach (eg, AQoL-4D measured at 0, 2 weeks, 1 month, and 6 months post-discharge). Patients may experience decline in QoL over time in both control and intervention groups for reasons unrelated to the intervention; a lesser magnitude of decline in intervention versus control group may suggest a benefit of the intervention.

For patients who do not complete a study follow-up, we will analyze all available data points. Additionally, understanding the characteristics (via collected demographic and administrative data of this study) of those who do not complete follow-up may inform us of under what conditions and for whom the technology works best.

Qualitative data will be analyzed using an ethnographic case study approach [86], adopting techniques such as interpretive descriptive coding methods and word tables [85] to support the within and cross case analysis as used in previous evaluations and similar case comparisons [33,48]. Two researchers trained in qualitative research will read interview and focus group transcripts and field notes, record key themes, compare, and discuss findings. Both inductive and deductive analysis techniques will be used to identify themes and then conceptually map with the CFIR theoretical framework. NVivo software (QSR International) will be used for qualitative data management.

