#### Phase 2: Economic Evaluation Analysis

A cost utility analysis will be conducted comparing total costs and quality-adjusted life years (QALYs) of Digital Bridge to usual care from the perspective of Canada’s health care system. Costs and utility values will be assessed over the study follow-up period. Analysis will conform to most recent Canadian guidelines for economic evaluation [89]. Responses to the AQoL-4D will be scored using preference weights, converting the 5 responses into a single summary index, where a score of 1 reflects perfect health and 0 is equivalent to dead [90]. QALYs will be estimated using total area under the curve methods [91]. Statistical analysis will be conducted in accordance with current guidelines for clinical and cost-effectiveness analysis alongside randomized controlled trials [92], accounting for the repeated nature of the cost and outcome data. The incremental cost and QALYs will be estimated using generalized estimating equations, a flexible multivariate regression framework that explicitly allows for the modeling of nonnormal distributional forms of repeated measure data. As we will have individual level data on costs and QALYs for the period of study follow-up, we will evaluate uncertainty of the cost utility estimates using nonparametric bootstrapping, obtaining 5000 estimates of costs and QALYs for each strategy. Bootstrapping results will also be used to estimate 95% confidence intervals and depict cost-effectiveness acceptability curves. These analyses represent the probability of an intervention being cost-effective to a range of potential threshold values that the health system may be willing to pay for an additional unit of effect. As a scenario analysis, we will also conduct a cost utility analysis from a societal perspective by including patient-related costs. Economic analysis will be conducted using Stata version 15.1 (StataCorp LLC) and Excel Visual Basic for Applications (Microsoft Corporation). Analyses will support a proposed model of scale and spread in the Ontario context and/or similar health system contexts in Canada based on patient volumes.

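### The cost-utility analysis claims costs and QALYs over one follow-up period, but costs run 1 year and utilities and patient costs stop at 6 months

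*Protocol article*

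**What the plan says.** All of the relevant text is in the protocol article.

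- **Cost horizon.** Under Developmental and Economic Evaluation Measures: "Control and intervention patients will be followed for 1 year", and "Health services utilization and health system costs will be measured for 1 year using province-wide health system administrative data". Table 1, under Value for money, agrees for the ICES data: "Utilization 1 year after discharge".
- **Utility schedule.** Table 1, under Patient (outcomes), lists the AQoL-4D "At 1 and 6 months post-discharge". The section Phase 2: Developmental Evaluation and Implementation Analysis gives a different schedule: "AQoL-4D measured at 0, 2 weeks, 1 month, and 6 months post-discharge". Both end at 6 months.
- **Patient costs.** In Table 1 the patient cost survey has the same timing, 1 and 6 months. The measures section defines total costs as system costs plus out-of-pocket costs.
- **Analysis.** Under Phase 2: Economic Evaluation Analysis: "Costs and utility values will be assessed over the study follow-up period"; "QALYs will be estimated using total area under the curve methods". The bootstrap is justified with "As we will have individual level data on costs and QALYs for the period of study follow-up". The base case there takes the health care system perspective, and a scenario adds patient-related costs.

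**The concern.** A cost per QALY can be interpreted only if incremental cost and incremental QALYs cover the same interval. The analysis section assumes that they do, but the measurement schedules do not supply such an interval. If follow-up means 1 year, the second half of the utility curve is unmeasured. If it means 6 months, the 1-year cost statements do not describe the inputs to the ratio. If the analyst simply uses all the data collected, the numerator and denominator cover different lengths of time.

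At stake are the incremental cost-effectiveness ratio and the acceptability curves, which are built from the same cost and QALY pairs. Cost-effectiveness is part of the second research question, and the section says that the economic analyses will support the scale-and-spread model.

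**Working it through.** The article reports no cost, utility or ratio, so there is no figure to reproduce. The check compares the schedules and then illustrates the effect with assumed values.

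**Step 1: coverage of the utility curve**

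The most QALYs one patient can accrue, at utility 1 throughout, is window length in months / 12.

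- Table 1 schedule (months 1 to 6): 5/12 = 0.417.
- Analysis-section schedule (months 0 to 6): 6/12 = 0.50.
- Year over which costs are counted: 12/12 = 1.00.

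Measured utilities therefore cover at most half of the costed year, and 5/12 of it under Table 1.

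**Step 2: incremental QALYs (assumed gain)**

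Assume a between-group utility gain of 0 at discharge, rising to d by week 2 and constant to month 6. Trapezoidal areas, in month units and divided by 12:

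- To month 6: (0.25 + 0.5 + 5)d/12 = 5.75d/12.
- To month 12, gain falling linearly to 0 from month 6: (5.75 + 3)d/12 = 8.75d/12.
- To month 12, gain sustained: (5.75 + 6)d/12 = 11.75d/12.
- To month 12, gain ending right after month 6: 5.75d/12.

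| d | To month 6 | To month 12, waning | To month 12, sustained |
|---|---|---|---|
| 0.02 | 0.0096 | 0.0146 | 0.0196 |
| 0.05 | 0.0240 | 0.0365 | 0.0490 |
| 0.10 | 0.0479 | 0.0729 | 0.0979 |

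**Step 3: cost per QALY**

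Assume an incremental 12-month cost of 1,000 and d = 0.05.

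- 12-month cost over 6-month QALYs: 1,000/0.02396 = 41,739.
- Matched at 12 months, waning: 1,000/0.03646 = 27,429. Factor 8.75/5.75 = 1.52.
- Matched at 12 months, sustained: 1,000/0.04896 = 20,426. Factor 11.75/5.75 = 2.04.
- Matched at 12 months, gain ending right after month 6: 41,739. Factor 1.0.
- Matched at 6 months, cost accruing evenly: 500/0.02396 = 20,870. Factor 2.0.
- Matched at 6 months, all incremental cost incurred by month 6: 41,739. Factor 1.0.

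The factors do not depend on d or on the 1,000. They depend on whether the gain persists after month 6 and, for a 6-month comparison, on when costs accrue. The article gives neither.

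**The case against.** **The mismatched ratio is not the stated plan.** A reader might infer that the trial will divide 12-month costs by 6-month QALYs and so double its cost per QALY. The text does not support that. The analysis section names one common period for costs and utilities and never describes such a division. What the text does support is that this common period has no stated length except 1 year, and that the claimed QALY data do not exist for 1 year. This objection stands and limits the point to that.

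**Collecting costs for a year is not an error.** Admissions, emergency visits and days in acute care are useful at 1 year without a QALY denominator. This also stands.

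**An extrapolation or truncation rule may sit in a fuller plan.** Its absence from an article is not a finding, and none is claimed. The conflict is among things the article does state: cost horizon, utility time points, QALY method and data coverage. A fuller plan could choose a horizon, but it could not create utilities that were not measured.

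**The two-fold figure is one scenario.** It needs the utility gain to persist through months 6 to 12. The article describes ePRO self-management support as lasting 6 months after discharge, so waning cannot be ruled out. This stands, and the range starts at 1.0. Nor can the figure be carried over to overstated savings per QALY: lower cost with a QALY gain is dominance, and the size of a negative ratio is not interpretable.

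**The patient-cost mismatch touches only a scenario.** That is correct under the analysis section, where the base case takes the health care system perspective.

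**Conclusion.** The point holds as an unreconciled horizon. On the only follow-up length stated, 1 year, area-under-the-curve QALYs cannot be computed from either AQoL-4D schedule, and the statement that individual costs and QALYs will be available for that period is unsupported. Using all collected data would mix 12-month system costs with 6-month QALYs and, in the societal scenario, with 6-month patient costs.

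The cost per QALY could be distorted. Under the assumed values the factor against a matched 12-month ratio runs from 1.0 through about 1.5 to about 2.0. These are illustrations, and the article does not determine the actual size.

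This should be fixed for the sake of the economic conclusion. It has no bearing on the primary outcome, CTM-3.

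**What to change.** 1. State one base-case cost-utility horizon, discharge to 6 months, for system costs, patient costs and QALYs, and truncate the dated ICES costs at 6 months.
2. Reconcile the two AQoL-4D schedules so that a baseline or discharge measurement anchors the area under the curve. Table 1 has no such time point, and without it a discharge-to-6-month QALY needs an assumption about the first month.
3. Report 12-month utilization and system costs as a separate cost analysis.
4. Present any 12-month cost per QALY only as a labelled scenario, with its utility extrapolation stated.

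The first, third and fourth changes are analysis wording, and truncating dated cost records needs no new data. The second is also wording if the discharge measurement is already planned. If Table 1 is the operative schedule, it adds one questionnaire per patient. The downside is a shorter base-case horizon. If the sponsor wants a 1-year base case, the alternative is to add a 12-month AQoL-4D and cost survey, which means more data collection and must be decided while patients can still be surveyed.
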